### Data management

Data will be collected during the participants’ visits to the hospital at baseline, 6 weeks, 3 months, 6 months and 1 year after random assignment (table 1). Reminder emails and phone calls from the research assistants will be programmed to maximise participant compliance in subsequent completion. A registered participant will withdraw from the study if (1) the participant withdraws his/her consent and (2) exclusion criteria is found after registration. The cause and date of suspension will be recorded. Consent to use data that has been collected before the participant’s withdrawal will be included in the consent form.

**Table 1 T1:** Study evaluation procedures and timeline

Study procedure	Medical evaluation	Enrolment visit	6 weeks	3 months	6 months	1 year
Determine eligibility	√	√				
Obtain signed consent		√				
Obtain medical and demographic data		√				
Give instructions for pain medication diary		√				
Outcome measures						
Boston Carpal Tunnel Questionnaire		√	√	√	√	√
Interrupted Sleep Questionnaire		√	√	√	√	√
European Quality of Life Scale (EuroQol)-5D		√	√	√	√	√
Hospital Anxiety and Depression Scale		√	√	√	√	√
Work Limitations Questionnaire-25		√	√	√	√	√
Treatment success rate			√	√	√	√
Treatment recurrence rate				√	√	√
Physical examination		√	√	√	√	√
Electrophysiological and ultrasound parameters		√	√	√	√	√

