#### Exclusion criteria

CTS secondary to wrist deformity, trauma, mass, pregnancy, hypothyroidism or inflammatory arthropathy.Treatment by night splint, therapeutic US or injection within the past 6 months or previous carpal tunnel surgery.Previous surgery on the affected wrist (or study wrist if bilateral CTS).Unable to tolerate the study interventions.Trauma to the affected upper limb requiring operation or immobilisation within the past 12 months.Current illness including, poorly controlled diabetes mellitus or thyroid disease, vibration-induced neuropathy, osteoarthritis or inflammatory joint disease, suspected complex neurological and musculoskeletal conditions.Known drugs or alcohol abuse.Allergy to any of the splint materials.Contraindications to therapeutic US, including dermatological conditions, abnormal sensation in the affected arm, indwelling electrical pumps/pacemakers, epilepsy, pregnancy or breast feeding.

Following the medical evaluation, a research assistant will meet with the eligible participants and obtain their written informed consent. Demographic variables such as age, sex, body mass index, affected wrist (whether bilateral), dominant arm, lifestyle (smoking and alcohol use) and medical history of all participants will be collected prior to treatment (baseline). Participants will also be asked relevant questions about symptoms duration and previous treatments (rehabilitation exercises, injections or others). Others like occupation, employment characteristics (full-time or part-time work, manual or non-manual labour), employment status (whether on sickness absence), and professional activity characteristics (repetitive movements for >4 hours/day; wrist flexion and extension for >2 hours/day and use of computer keyboard/mouse (how many hours/day)) will be also collected.

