
### Adverse events

All adverse events, defined as any negative or unwanted reactions to intervention, will be recorded through the symptoms reported by the patients, and observations by a researcher at every visit. Therapeutic US may cause mild local swelling, spot-like bleeding, ecchymosis, enhanced local pain response and local hyperesthesia or decrease. Night splint may cause skin allergy, wrist stiffness, etc. The participants will be instructed to do gentle range-of-motion exercises when removing the splint to prevent stiffness and reinforced adherence by verbal instruction.

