### Analysis plan

Baseline characteristics of the three treatment groups will be summarised using appropriate descriptive statistics. Both the primary and secondary analyses will be blind analyses of treatment assignments and will be performed using the intention-to-treat^55^ method, with all randomised participants retaining their original assigned group. Multiple imputation by chained equations will be used to address missing data caused by lost access and non-response if these missing data are judged to be random.

The primary comparisons for BCTQ-SSS scores will be made using linear regression. In secondary analyses, repeated measures mixed model^56^ will also be used to examine the associations between treatments and repeated outcome measures, with terms of treatment, time, trial centre and corresponding baseline values as covariates (age, gender, body mass index, etc). Bonferroni method will be used to adjust for multiplicity.^57 58^ Linear regression will be used for numerical outcomes, and logistic/ordinal regression for any categorical outcomes.

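### Withdrawing participants from the study when an exclusion criterion is found after registration can discard primary outcomes that the intention-to-treat analysis needs

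*Protocol article*

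**What the plan says.** Data management gives the withdrawal rule: "A registered participant will withdraw from the study if (1) the participant withdraws his/her consent and (2) exclusion criteria is found after registration". Staff are to note when and why this happened. On the use of data the section adds: "Consent to use data that has been collected before the participant’s withdrawal will be included in the consent form". Nothing is said about follow-up after withdrawal.

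The Analysis plan promises intention-to-treat, "with all randomised participants retaining their original assigned group". Multiple imputation is to be used for "missing data caused by lost access and non-response if these missing data are judged to be random".

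The primary outcome is the BCTQ-SSS at 6 weeks (Primary outcome measure). Treatment in every arm also lasts 6 weeks (Intervention). Table 1 schedules the questionnaire at enrolment and then not before 6 weeks.

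**The concern.** The rule takes people out of the study, and so out of data collection, after they have been registered and most likely randomised. Intention-to-treat needs the outcome of every randomised participant, including those who should not have been enrolled. A rule that stops collection for some of them creates missing primary outcomes that the trial could have had.

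The loss may also be unequal. The exclusion criteria include intolerance of the interventions, skin conditions and altered sensation in the arm, and some of these could also appear during treatment. Participants and treating surgeons know the allocation (Strengths and limitations), so clause (2) leaves room for judgement after allocation is known. If those withdrawn would have done worse than the rest of their arm, that arm looks better than it should.

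**Working it through.** **1. Reach of the rule.** Clause (2) contains no words such as 'present before randomisation'. 'Registered' is not defined. Randomised is the likeliest reading, because a person found ineligible before allocation would simply not be allocated.

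**2. What is lost.** The BCTQ-SSS is measured at baseline and next at 6 weeks. A participant withdrawn between these visits has a baseline value, no primary outcome and no intermediate value to inform imputation. The imputation sentence names loss of access and non-response. A withdrawal that the protocol itself requires is neither.

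**3. Which criteria could arise on treatment, and in which arm.**
- "Unable to tolerate the study interventions" is an exclusion criterion. People treated with a splint or therapeutic ultrasound in the past 6 months are also excluded, so intolerance may not be known at entry.
- Skin conditions and altered sensation in the arm are listed as contraindications to ultrasound. The Adverse events section lists local swelling, ecchymosis and raised or reduced local sensation as possible ultrasound effects. In the primary contrast only the combined arm receives ultrasound.
- "Allergy to any of the splint materials" is an exclusion criterion, and the Adverse events section says "Night splint may cause skin allergy, wrist stiffness, etc". Both arms of the primary contrast wear a splint, so this trigger does not separate them. It is asymmetric only in comparisons with ultrasound alone.

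**4. Size.** The plan gives no rate for withdrawals of this kind. Its nearest figure is the general drop-out allowance: 48 / 0.90 = 53.3, rounded up to 54 per arm, which is 6 participants per arm and 3 × 54 = 162 in total. This reproduces. The 48 is used below only to set the scale.

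Inputs from Sample size calculation: SD 0.76, 48 evaluable per arm, margin 0.8, assumed true difference 1.19. Assumptions of this review: a fraction f of 5–10% of one arm is withdrawn under clause (2), none in the other arm, and those withdrawn would score d = 0.5–1 SD worse (0.38–0.76 points) than the rest of their arm.

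If the rest of the arm has mean m, the full arm has mean (1 − f)m + f(m + d) = m + fd. Dropping these participants shifts the arm mean by fd in its favour.

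- SE of the contrast = 0.76 × √(2/48) = 0.155
- f = 0.05, d = 0.38: 0.019 points, 0.019 / 0.155 = 0.12 SE
- f = 0.05, d = 0.76, or f = 0.10, d = 0.38: 0.038 points, 0.24 SE
- f = 0.10, d = 0.76: 0.076 points, 0.49 SE

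The gap between the assumed true difference and the margin is 1.19 − 0.8 = 0.39. The shift is 0.019 / 0.39 = 5% to 0.076 / 0.39 = 19% of that gap.

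**The case against.** The strongest reply is that the rule and the analysis can be read together. Data management ends participation but does not say that the person leaves the analysis. It keeps earlier data, and the Analysis plan retains everyone randomised. This stands: a reader might infer a flat contradiction of intention-to-treat, but the text supports only a loss of outcomes.

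Second, a criterion 'found' after registration may simply be a pre-existing condition discovered late. Table 1 marks eligibility only at the medical evaluation and the enrolment visit, and the Adverse events section records events without attaching withdrawal to them. This also stands. Removal for treatment-caused events is a possible reading, not a stated rule. Nor do these criteria come to light only through treatment: allergy may be known from history, and altered sensation may be found at the eligibility examination. It does not rescue the clause, because stopping follow-up for a pre-existing condition found late also loses the 6-week outcome.

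Third, a reader might infer that poor responders are removed selectively. No exclusion criterion concerns response or worsening of symptoms, and intolerance is not poor response.

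Fourth, the size is assumed. One could turn the upper end into an error rate on the favourable side: P(Z > 1.96 − 0.49) = 7% instead of 2.5%. That needs 10% of one arm lost under this clause alone, none in the other, a full SD worse outcome, and nothing recovered by imputation or covariates. At the lower end P(Z > 1.84) is about 3.3%. The 7% should not be quoted as the expected effect.

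Finally, sensitivity analyses for missing data commonly belong in a statistical analysis plan, which is not shown. Their absence from the article is not part of this point.

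**Conclusion.** The concern holds in a limited form. The withdrawal rule is stated, not merely left open. If it is followed during the treatment period, it discards primary outcomes of participants whom the plan intends to analyse, and the imputation wording does not cover them. The loss could be unequal between the combined and splint arms through the ultrasound-related criteria and intolerance, not through splint allergy. If those withdrawn from the combined arm would have done worse, the bias favours that arm.

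On the stated assumptions the bias is about 0.02–0.08 points, or 0.12–0.49 SE: small against the 0.39-point gap, but systematic. The actual rate and direction are unknown. The conclusion assumes that 'registered' means randomised and that the two clauses, although joined by 'and', are alternatives.

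This should be fixed, and before anyone is withdrawn under the rule, because a 6-week outcome that was not collected cannot be recovered. The case rests on the avoidable loss of outcomes, not on a demonstrated bias.

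**What to change.** Replace clause (2) in Data management with wording such as: *Eligibility is judged on status before randomisation. A participant found ineligible after randomisation stays in scheduled follow-up and in the intention-to-treat analysis in the assigned group. Only withdrawal of consent ends data collection. Decisions about continuing treatment are separate and do not by themselves end study participation.* This point makes no proposal about those treatment decisions.

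In the Analysis plan, extend the multiple imputation wording to any missing primary outcome, whatever the reason.

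The cost is two changes of wording and a few follow-up visits that Table 1 already schedules. The sample size does not change.

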### Primary outcome measure

The primary outcome measure will be the difference in Symptom Severity Scale of the Boston Carpal Tunnel Questionnaire (BCTQ-SSS) at 6 weeks. The BCTQ is a disease-specific questionnaire referring to a typical 24-hour period in the past 2 weeks,^35^ and has been shown to be highly reproducible, internally consistent, valid and responsive to clinical change in CTS.^36^ It consists of two different subscales: Symptom Severity Scale (11 items, about symptom severity) and Functional Status Scale (8 items, about the degrees of difficulty on daily activities), both rated on a five-point scale, with final scores for each subscale result in mean scores between 1 and 5. The overall score is calculated as the mean of all 19 items. Higher scores represent more severe symptoms and functional impairment. We use a validated Chinese version^37^ of the BCTQ in this study.

### Secondary outcome

Secondary outcome measures will be the differences in Functional Status Scale of the Boston Carpal Tunnel Questionnaire (BCTQ-FSS), sleep questionnaire for interrupted sleep,^38^ European Quality of Life Scale (EuroQol)-5D (EQ-5D)^39^ for life quality and health status, Hospital Anxiety and Depression Scale (HADS)^40^ for anxiety and depression status, Work Limitations Questionnaire (WLQ)-25^41^ for functional limitations at work, Global Rating of Change (GROC) for treatment success and recurrence rate, physical function examination as well as various electrophysiology and US parameters.

Interrupted sleepThe sleep questionnaire, which will be used to assess sleep quality, consists of four questions asking participants how many times they have experienced it in the last month.^38^ Each question has six response categories and are coded in 0–5 order: not at all, 1–3, 4–7, 8–14, 15–21 and 22–31 days. All questions have equal weights and add up. Higher scores are associated with more disrupted sleep.Life quality and health statusEQ-5D has been widely validated and used to measure generic health-related quality of life (HRQol) due to its simplicity.^39^ It consists of a five-dimensional description system (mobility, self-care, usual activities, pain/discomfort and anxiety/depression) and a visual analogue scale that scales from 0 to 1, where 1 represents perfect health. All dimensions are divided into three levels (no problem, some problem and extreme problem). We used a validated Chinese version^42 43^ of EQ-5D, which has been recommended by Guidelines for Pharmacoeconomic Evaluations 2011 for a measure for HRQol and health utility.^44^Anxiety and depression statusHADS will be used to identify and quantify two of the most common psychological disorders - anxiety and depression.^40^ There is evidence of increased anxiety and depression in LET patients.^45^ The HADS is a 14-item scale independent of physical symptoms and consists of two 7-item subscales measuring depression and anxiety, respectively. A four-point scale (0 for absence of symptoms and 3 for maximum symptomatology) is used. Each subscale has an overall score ranging from 0 to 21, with a higher score indicating a higher degree of impairment. HADS has two cut offs for categorisation: 0–7, ‘non-case’; 8–10, ‘possible or doubtful case’; 11–21, ‘probable or definite case’.^46^Functional limitations at workTo gather information that is complementary to the pain and disability scales, functional limitations at work will be measured using WLQ-25. It contains 25 items, arranged under four subscales, covering four dimensions of job demands, namely time demands, physical demands, mental/interpersonal demands and output demands.^41^ A five-level ordinal response scale ranging from 0 (all of the time) to 4 (none of the time) with an additional sixth option (does not apply to my job) is used. The overall score ranges from 0 to 100, with an increase of 13 points (out of 100) for clinically important differences.^47^Treatment success and recurrence rateParticipants’ treatment impressions of changes in their condition (ranging from ‘completely recovered’, ‘much improved’, ‘somewhat improved’, ‘same’, ‘worse’ to ‘much worse’) will be recorded on a six-level Likert scale. The success rate will be calculated by dichotomising the response. Participants who report ‘completely recovered’ or ‘much improved’ in their overall condition since the study beginning will be considered successful, while other responses will be considered failures.^48 49^ Recurrence will be defined primarily as when a participant rates a success at 6 weeks and a failure at 3 months, 6 months or 1 year on GROC.^48 49^Physical function examinationThe physical examinations will include measurement of two-point discrimination (performed on the radial and ulnar aspects of each digit), grip strength with a dynamometer (CAMRY, City of Industry, California, USA), and pinch strength with the pinch gauge (three trials for each hand). The affected side will be measured first and then the unaffected side. The measurement readings will be not revealed to the subjects until the completion of the test. The mean of three consecutive trials, separated by a 20 s pause, will be calculated. Results will be presented as a ratio of values of the symptomatic side/asymptomatic side ×100.^50^The two-point discrimination test starts at a distance of 4 mm and increases continuously by 2 mm as necessary. Grip strength and three-point pinching force (three tests per hand) as measured with baseline dynamometer and pinch gauge (Chattanooga Group, Hixson, Tennessee, USA) will be recorded.Electrophysiological studyMedian nerve distal motor latency (DML), compound muscle action potential (CMAP), sensory nerve conduction velocity (SNCV) and sensory nerve action potential (SNAP) amplitudes will be recorded.^48 49^ DML and CMAP will be measured by placing surface electrodes on the abductor pollicis brevis muscle, and stimulation applied 8 cm proximal to the active recording electrode. SNAP and SNCV will be obtained using ring electrodes placed on the proximal and distal interphalangeal joints of the index finger. Sensory conduction will be studied by antidromically stimulation at 14 cm proximal to the active electrode. Motor study will be performed by supramaximal stimulation while the amplitude will be measured an average of 10 times for the sensory study. All measurements will be made three times, and the values obtained will be averaged for analysis.US parametersThe cross-sectional area will be measured using an electronic calliper at the scaphoid-pisiform level.^51 52^ The measurements will be made three times, and the values obtained will be averaged for analysis.

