#### Inclusion criteria

Age ≥18 years old.Clinical diagnosis on the basis of clinical symptoms, history and physical examination, using criteria developed from a consensus survey by the UK Primary Care Rheumatology Society.^31^Mild to moderate CTS,^9^ with symptoms longer than 6 weeks duration; participants with bilateral CTS will be designated their study hand based on the most severe symptoms.Mild: intermittent paraesthesia in the distribution of the median nerve.Moderate: constant paraesthesia, and reversible numbness or pain of idiopathic nature.Severe: constant pain, numbness or sensory loss in the wrist and hand (specifically palm, index, or middle finger, or thumb), or thenar muscle atrophy.Able to read and write in simplified Chinese (Mainland), understand and complete the questionnaire, and should provide informed consent.

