### Intervention

At the beginning, all participants will participate in an about 30 min group educational presentation by a research assistant on the same day as the baseline assessment. This presentation will cover the pathophysiology, treatment options, posture and activity modification principles of CTS. The above information will also be provided to participants in the form of education booklets, to encourage them to review at home. Habits changes include limited wrist movement and a reduction in strenuous work activities, and the use of ergonomically friendly work tools helps reduce median nerve pressure.^32 33^

Participants in the (therapeutic US group) will receive pulsed therapeutic US (model 1:4, Shanghai, China) for 6 weeks at a frequency of 1 MHz and intensity of 1.0 W/cm^2^ for 15 min per session, in daily five times a week for the first 2 weeks and twice a week for another 4 weeks, to the area over the carpal tunnel, referred to a published trial (BMJ. 1998;316:731–735).

Participants allocated to the (night splint group) will receive a splint to wear at night for 6 weeks, referred to a published trial (Lancet. 2018;392:1423–1433). The splint holds the wrist in a neutral position or slightly extended 20° from the neutral position to avoid wrist movement, which can increase pressure on the carpal tunnel.^34^ The choose of each splint will be based on the size of individual participant’s hands and arms. Participants will be shown how to fit and remove the wrist splint according to a standardised trial protocol. Oral guidance from the clinician on how and when to use splints will encourage and reinforce compliance, which will be also supported by written information, detailed care and splint fitting and use. Participants will be instructed to perform gentle range-of-motion exercises when removing the splint to prevent stiffness.

Participants randomised to the (therapeutic US+night splint group) will receive both therapeutic US for 6 weeks as in the (therapeutic US group) and night splint for 6 weeks as in the (night splint group).

For participants with bilateral CTS, the non-study hand will be treated according to normal clinical protocols in use at the research site.

We discouraged additional treatments to that assigned (ie, not per protocol) during the intervention period, but we allowed the use of simple analgesics as needed. Participants reported all not per protocol treatments, such as drugs, in a diary.

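### The side-to-side ratio for strength has no valid denominator in participants with bilateral carpal tunnel syndrome

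*Protocol article*

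**What the plan says.** All of this comes from the protocol article.

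- **Secondary outcome, physical function examination.** The examination covers two-point discrimination, grip strength and "pinch strength with the pinch gauge (three trials for each hand"). On order: "The affected side will be measured first and then the unaffected side". On scale: "Results will be presented as a ratio of values of the symptomatic side/asymptomatic side ×100".
- **Secondary outcome, opening list.** The measures to be compared include "physical function examination as well as various electrophysiology and US parameters", so this is a secondary outcome and not only a background description.
- **Inclusion criteria.** Bilateral disease is eligible: "participants with bilateral CTS will be designated their study hand based on the most severe symptoms".
- **Exclusion criteria and baseline data.** Nobody is excluded for bilateral disease. Laterality is collected at baseline as "affected wrist (whether bilateral").
- **Intervention.** "For participants with bilateral CTS, the non-study hand will be treated according to normal clinical protocols in use at the research site".
- **Analysis plan.** All randomised participants are analysed in their assigned group, and numerical outcomes are analysed by linear regression.

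No section gives a different denominator for bilateral participants, limits the outcome to unilateral cases, or names the study-hand value itself as the analysed quantity.

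**The concern.** A side-to-side ratio is meant to use the healthy hand as the participant's own reference. It works when one hand is healthy and stays roughly constant. A participant with bilateral disease has no such hand. Read literally, the outcome is undefined for that participant. Read practically, with the non-study hand as reference, the denominator is a symptomatic hand that may change through its own disease course and through treatment that was not randomised.

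What is at stake is the meaning and precision of the comparison of arms on grip and pinch strength, and probably on two-point discrimination. The protocol states both the scale and the eligibility and treatment rules under which the scale fails, so this is a conflict between stated rules and not missing detail.

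**Working it through.** The plan gives no expected value, SD or sample size for this outcome, so there is no figure to reproduce. The check has two parts.

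**1. Does the stated definition apply to everyone enrolled?**

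The scale needs one symptomatic and one asymptomatic side. The inclusion criteria admit people with two symptomatic sides and only name which one is the study hand. The denominator therefore does not exist for them as written. Multiple imputation, which the Analysis plan provides for loss to follow-up and non-response, does not help: the value is undefined, not missing.

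**2. What happens if the non-study hand is used as denominator?**

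Inputs, all assumed for illustration because the document gives none:
- baseline ratio R0 = 80;
- proportional gain of the study hand, g = 20% in arm A and 10% in arm B;
- proportional gain of the other hand, c, varied.

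Follow-up ratio = R0 × (1 + g) / (1 + c).

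If c is the same in both arms, contrast = R0 × (gA − gB) / (1 + c).

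| Other hand, arm A / arm B | Ratio A | Ratio B | A − B |
|---|---|---|---|
| unchanged / unchanged | 80 × 1.20 = 96.0 | 80 × 1.10 = 88.0 | 8.0 |
| +10% / +10% | 96 / 1.1 = 87.3 | 88 / 1.1 = 80.0 | 7.3 |
| +20% / +20% | 96 / 1.2 = 80.0 | 88 / 1.2 = 73.3 | 6.7 |
| +20% / +10% | 96 / 1.2 = 80.0 | 88 / 1.1 = 80.0 | 0.0 |
| +10% / +20% | 96 / 1.1 = 87.3 | 88 / 1.2 = 73.3 | 13.9 |

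Rows 2 and 3 show the shared-gain case: the contrast shrinks by 1/(1+c), so 1/1.2 = 83% survives at c = 20%. Rows 4 and 5 show that a gain differing by arm can hide or inflate the contrast.

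**Over the whole sample.** The bilateral share b is not stated. If it were 30% to 60%, that would be 0.30 × 162 = 48.6 to 0.60 × 162 = 97.2, or about 49 to 97 participants. With a shared c of 20%, the mean contrast would be (1 − b) × 8.0 + b × 6.67:
- b = 30%: 5.6 + 2.0 = 7.6 points;
- b = 60%: 3.2 + 4.0 = 7.2 points.

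**A limit of this arithmetic.** It holds R0 at 80 for everyone. Against a diseased reference hand, R0 may well be higher, which scales the contrast up: at R0 = 100 the contrast is 100 × 0.10 = 10.0 points with c = 0 and 10.0 / 1.2 = 8.3 with c = 20%. So a point on the ratio does not mean the same thing in unilateral and bilateral participants.

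**The case against.** **The treatment effect is not cancelled.** A reader might infer cancellation from a before-and-after example: study hand 20 to 24 kg, other hand 25 to 30 kg, ratio 80% both times. That is a change within one patient. The trial compares arms, and a contralateral gain common to the arms only rescales the contrast. Full cancellation needs the other hand's gain to differ between arms in step with the study hand's, and the Intervention section does not tie that hand's care to allocation. This objection stands. What is left is dilution, noise and a possibility of bias.

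**The other hand's care is not off-protocol.** The protocol itself provides for it. It is unrandomised, which is the relevant point.

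**The measurement order is workable.** The exclusion criterion on earlier wrist surgery already equates the affected wrist with the study wrist in bilateral disease, so study hand first, other hand second is a natural reading. That settles the order of testing. It does not make the other hand asymptomatic.

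**Two-point discrimination may not be covered.** The ratio sentence directly follows the averaging of three trials, which fits grip and pinch. Discrimination is in the same paragraph and the sentence is unrestricted, so its inclusion is likely but not certain.

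**Intention-to-treat is not broken as written.** No section proposes dropping bilateral participants. Dropping them would depart from the stated population and cost precision; since laterality is a baseline feature, it need not bias the comparison.

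**The analysis plan could resolve it.** The article says results are presented as a ratio, and also that the forces are recorded, so an unseen document might analyse raw values. That is possible, but the only scale the article states is one that fails for an eligible group.

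**A narrower remedy exists.** Stating a denominator rule for bilateral participants would remove the wording conflict. It would still leave a treated, diseased hand in the outcome.

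**Conclusion.** The point holds in a limited form. For participants with bilateral disease the stated ratio has no valid denominator, and this follows from the protocol's own sections at any bilateral share above zero.

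If the non-study hand stands in, three consequences follow:
- the denominator adds variation unrelated to the randomised treatment of the study hand;
- a gain shared by the arms dilutes the contrast by 1/(1+c) at a given baseline ratio, for example from 8.0 to 6.7 points at c = 20%;
- bias is possible if care of the other hand differs by arm. Participants and treating surgeons are unblinded and that care follows local routine, but nothing in the document shows that it will differ.

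The sizes rest on assumed baseline ratios and gains, and the bilateral share is unknown. The ratio remains well defined in unilateral cases. The outcome is one of several secondary measures; the primary BCTQ-SSS comparison and the sample size are unaffected. It should be corrected, but it does not threaten the trial's main conclusion.

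**What to change.** State that, for all randomised participants, grip and pinch strength are analysed as the study-hand value in physical units at each visit, adjusted for that hand's own baseline. Do the same for two-point discrimination in millimetres, and say explicitly whether the ratio was meant to cover it. Keep the side-to-side ratio as a descriptive summary in unilateral cases only. In the measurement instruction, replace affected and unaffected with study hand and other hand.

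The cost is wording. The hands are already measured, Table 1 schedules the physical examination at enrolment and at every follow-up visit, and bilateral status is recorded at baseline. No extra data are needed and no treatment rule changes.
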